## Abstract

Long-acting (LA) injectable therapy as treatment for HIV-1 infection offers reduced dosing frequency, increased discretion and provides an alternative to two or three-drug daily oral combinations. A parenteral LA formulation of cabotegravir (CAB) and rilpivirine (RPV) given by intramuscular (IM) injection every 2 months (CAB LA + RPV LA Q2M) has shown safety and efficacy in phase 3/3b trials and could increase treatment satisfaction and improve adherence in sub-Saharan Africa.

IMPALA (IMProving HIV-1 Control in Africa using Long-Acting Antiretrovirals) is a randomized, controlled, open-label, multicentre, interventional study in Uganda, Kenya, and South Africa of 540 virologically suppressed adults living with HIV-1 infection with a history of sub-optimal adherence to daily oral ART . IMPALA seeks to demonstrate the non-inferior antiviral effectiveness of switching to CAB LA + RPV LA Q2M, compared to the continuation of first-line daily oral ART containing 2 nucleoside/nucleotide reverse transcriptase inhibitors (NRTIs) plus dolutegravir (DTG). After providing informed consent, participants are screened for eligibility. Those who are viraemic (HIV RNA ≥200 copies/mL) at screening will be suppressed (<200 copies/mL for ≥3 months) on oral ART prior to randomization. On Day 1, individuals will be randomized 1:1 to either continue daily oral ART, or switch to CAB LA + RPV LA Q2M, (intervention arm) with or without a 1-month oral lead consisting of once daily oral CAB + RPV. The total follow-up period is 24 months. The primary endpoint is HIV-1 RNA <50 copies/ml at 12 months by FDA snapshot.

Initial: TMC278LAHTX3005 Version Amendment 1, 30 September 2022

Superseded by: TMC278LAHTX3005 Version Amendment 2, 3 June 2024

This clinical trial was registered on Clinical Trials.gov on 19 September 2022 (NCT05546242), available from
https://clinicaltrials.gov/ct2/show/NCT05546242.

The study was also registered on Pan African Clinical Trials Registry on 23 January 2023 (PACT202301600757432TMC278LAHTX3005), available from
https://pactr.samrc.ac.za/TrialDisplay.aspx?TrialID=24291.

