### Study procedures

Study participants will undergo several clinical and laboratory assessments, complete various questionnaires and participate in qualitative interviews, as detailed in the schedule of activities (SoA) (
Table 2).

**Table 2. T2:** IMPALA Trial Schedule of Activities.

Phase	Screening period ^ a ^		Optional OLI ^ b ^		Initiation (Months)	Maintenance Phase (Months)															
Period	SCR 1	SCR 2 ^ a ^	Baseline	1	2	3	4	6	8	9	10	12	14	15	16	18	20	21	22	24 ^ c ^	Unscheduled Visit ^ t ^
**Visit Window (days)**			**±8**	**±7**																	
Study visits – vary by arm, activities listed below only apply if the participant has a visit scheduled in line with their randomization arm																					
CAB LA + RPV LA			X	X	X		X	X	X		X	X	X		X	X	X		X	X	X
cART	X	(X) ^u^	X			X		X		X		X		X		X		X		X	
Clinical assessments and procedures																					
Informed consent / assessment of understanding	X																				
Administration of oral CAB and RPV			X ^ b ^																		
Administration of IM CAB/ RPV ^ d ^				X	X		X	X	X		X	X	X		X	X	X		X	X	X
Chest Xray, ECG	X																				
Assessment of eligibility	X	(X) ^u^																			
Medical history and demographics	X																				
Adherence assessment ^ e ^	X	(X) ^u^	X	X		X		X		X		X		X		X		X		X	X
Con-meds	X	X	X	X	X	X	X	X	X	X	X	X	X	X	X	X	X	X	X	X	X
Vital Signs	X	X	X	X	X	X	X	X				X				X				X	X
Physical examination	X		X					X				X				X				X	
ISR assessment				X	X		X	X	X		X	X	X		X	X	X		X	X	X
AE assessment ^ f ^	X	X	X	X	X	X	X	X	X	X	X	X	X	X	X	X	X	X	X	X	X
Weight and appetites	X		X					X				X ^ s ^				X				X ^ s ^	
Height			X																		
EuroQoL-SD-SL			X					X				X								X	
MOS-HIV			X					X				X								X	
HIVTSQs			X					X													
HIVTSQc												X								X	
Treatment preference												X								X	
Medical resource utilization and patient-related outcomes																					
MRU			X									X ^ g ^				X					
In-depth interviews ^ h ^			X					X				X									
OLI questionnaire (LA arm only)			X																		
Blood and urine tests																					
HIV-1 RNA ^ i, j ^	X	(X) ^ iu^	X		X ^ k ^	X ^ l ^		X	X ^ k ^	X ^ l ^		X				X				X	
CD4+ count	X		X					X				X				X				X	
Hepatitis B serology (HBcAb, HBsAg, HBsAb)	X											X ^ r ^								X ^ r ^	
Hepatitis C serology (HCV Ab)	X																				
CBC, Biochemistry ^ m ^	X		X		X	X	X ^ q ^	X				X				X				X	
HbA1c, fasting lipids			X									X								X	

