**Footnotes:**
a. Screening visit 2 is only required if HIV-1 VL ≥200 at screening visit 1 or duration of virologic suppression (HIV-1 VL <200 c/mL) has not reached 3 months. Once a participant is confirmed as virologically suppressed (<200 c/mL), and duration is ≥3 months then randomization should occur within 2 weeks. The screening period must be completed within 4 months. a. One month of oral CAB and RPV (OLI) or continue daily oral ART (DTI) prior to first injections of CAB LA + RPV LA at month 1. b. Perform Month 24 assessments in all participants who withdraw from study intervention prematurely (if participant is willing), and scheduled assessments off the study intervention should be continued up to the Month 24 visit as specified in Section 7.1, Discontinuation of Study Intervention. c. For participants with BMI ≥30 a longer needle should be used as per product administration instructions. d. Adherence assessment and tablet count only in participants receiving daily oral ART, or oral lead-in/bridging treatment in CAB LA + RPV LA group. e. Clinical AEs will be captured from the time of screening. Laboratory abnormalities will not be recorded/reported as AEs till after the baseline visit. f. Detailed healthcare resource data survey to be performed at Month 12 visit, at selected sites only g. From a purposively selected sample at selected sites. h. HIV-1 VL can be repeated on one additional occasion after screening visit 1 if it is still ≥200 c/mL. i. Additional HIV-1 VL testing is performed after 4 (3–6) weeks in participants with VL ≥200 c/mL in CAB LA + RPV LA group; additional plasma sample stored (for batched, blinded viral load testing) after 4 (3–6) weeks in participants with VL ≥200 c/mL in the cART arm; and additional viral load after 12 (10–14) weeks in participants with viral load ≥1000 c/mL in the cART arm; reflex resistance testing is performed on stored plasma sample in participants with VL ≥200 c/mL in the CAB LA + RPV LA group, or ≥1000 c/mL in the cART group. (See also Section 8.1.1.2 for an alternative threshold for testing and definition of virologic failure in the cART group) Pregnant participants in the CAB LA + RPV LA arm who continue the study should have viral load monitoring frequency increased to every 2 months aligned with CAB LA + RPV LA Q2M injection visits during pregnancy and for 6 months following delivery or more frequently as per treating physician preference. Repeat HIV-1 VL testing should be performed after 2–3 weeks in pregnant participants with VL ≥50 c/mL. j. CAB LA + RPV LA arm only k. cART arm only l. Complete blood count: hemoglobin, total white cell count and differential, neutrophil count, platelets. Biochemistry: creatinine, sodium, potassium, alanine transaminase, alkaline phosphatase, total bilirubin, aspartate aminotransferase (at screening only). For individuals switched from NNRTI to dolutegravir during the screening period national guidelines should be followed regarding glycemic monitoring before and after switch. m. Only required for females of reproductive potential n. PBMC stored for baseline archived genotypic drug resistance testing. o. One large size (8–10 mL) EDTA sample stored at the following time-points: at screening, baseline visit, all visits where HIV VL is performed, and each visit where the blood is taken for confirmation of viral load rebound (for additional resistance testing, pharmacokinetic analysis, immune or biomarker tests; both arms); at 1, 3, 6, and 12 months following cessation of CAB LA + RPV LA in participants who develop TB (for drug levels; CAB LA + RPV LA group only); at 1

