### Clinical assessment

Participants have vital signs including respiratory rate, heart rate and blood pressure measured at each visit during the screening period and the first six months of the study. These measurements are then taken again at Months 12, 18 and 24. Height is measured at the baseline visit to enable body mass index (BMI) calculations, and weight is measured at screening, baseline and Months 6, 12, 18 and 24.

At every visit, participants are assessed for any interim AEs. All clinical AEs are recorded from the first screening visit onwards, while asymptomatic laboratory AEs are reported from after baseline onwards. Post-injection reactions are considered AEs of special interest and will be recorded as such.

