### Qualitative methods sub-study

As shown in the SoA, participants complete questionnaires on quality of life
^
18,
19
^ and treatment satisfaction
^
20
^ at baseline and at Months 6, 12 and 24. Additionally, participants in the CAB LA + RPV LA arm answer a single question regarding treatment preference at Months 12 and 24. All participants are asked to complete a brief questionnaire about medical resource utilisation at months 12 and 18 to support health economic analysis. A brief questionnaire regarding the choice of OLI versus DTI will be administered at baseline to all participants randomised to the CAB LA + RPV LA arm.

In-depth interviews are conducted with a subset of 10–20 individuals from both Uganda and South Africa, at baseline, Month 6, and Month 12. Participants provide separate consent to participant in this qualitative sub-study. Additionally, up to 15 individuals who experience virological failure in the CAB LA + RPV LA arm will be approached to participate in a single in-depth interview, using a separate participant information sheet and consent form.

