### Objectives and endpoints

The objectives and endpoints of the Study are shown in
Table 3.

**Table 3. T3:** Study Objectives and Endpoints.

Objectives	Endpoints
Primary:	
To demonstrate the non-inferior efficacy of switching to every 2 months (Q2M) intramuscular (IM) injection of cabotegravir (CAB) long-acting (LA) plus rilpivirine (RPV) LA compared with continuation of daily oral ART over 12 months in people living with HIV-1 (PLHIV1) with a history of sub-optimal ART adherence or engagement in care	• Proportion with plasma HIV-1 viral load (VL) <50 c/mL at 12 months (by Food and Drug Administration [FDA] snapshot algorithm)
Secondary:	
To demonstrate the antiviral activity and the impact on retention in HIV care of switching to Q2M CAB LA + RPV LA compared with continuation of daily oral ART over 12 and 24 months in PLHIV1 with a history of sub-optimal ART adherence or engagement in care	• Proportion with confirmed virologic failure (CVF) [plasma HIV-1 VL ≥200 c/mL on 2 consecutive occasions] at 12 and 24 months • Proportion with LTFU [>4 weeks elapsed since their last missed appointment] at 12 and 24 months • Proportion with plasma HIV-1 VL <200 c/mL at 12 months by FDA snapshot algorithm • Proportion with virologic response [plasma HIV-1 VL <50 c/mL] at 24 months by FDA snapshot algorithm • Proportion with virologic non-response [plasma HIV-1 VL ≥50 c/mL] at 12 and 24 months by FDA snapshot algorithm
To demonstrate the immunological activity of switching to Q2M CAB LA + RPV LA compared with continuation of daily oral ART over 12 and 24 months in PLHIV1 with a history of sub-optimal ART adherence or engagement in care	• Change in CD4+ T cell count from baseline (12 and 24 months) • Incidence of HIV disease progression (HIV/AIDS-related hospitalizations, illness, or deaths) (through 24 months)
To evaluate the safety and tolerability of switching to Q2M CAB LA + RPV LA compared to continuation of daily oral ART	• Incidence of adverse events through 12 and 24 months • Incidence of adverse events, Grade 3 and 4 (through 12 and 24 months) excluding injection site reactions (ISRs) • Frequency of ISRs of any grade

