To assess genotypic viral resistance in participants experiencing protocol-defined CVF (confirmed plasma HIV-1 RNA ≥200 c/mL on 2 consecutive tests) and its impact on future treatment options including proportion who resuppress on dolutegravir	• Frequency of emergence of new integrase strand transfer inhibitor (INSTI) and non-nucleoside reverse transcriptase inhibitor (NNRTI) drug resistance mutations in those who develop virologic failure (through 12 and 24 months)
Exploratory	
To evaluate the effect of Q2M CAB LA + RPV LA on health-related quality of life	• Change from baseline in EQ-5D-5L at Month 12 and Month 24 • Change from baseline in MOS-HIV at Month 12 and Month 24 • Quality of life outcomes of in-depth interviews
To assess treatment satisfaction	• For participants in the CAB LA + RPV LA group, change from baseline in HIVTSQ scores at Month 6, Month 12 and Month 24
To assess preference for Q2M CAB LA + RPV LA compared to daily oral ART	• For participants randomized to the CAB LA + RPV LA group, preference for CAB LA + RPV LA compared to daily oral ART regimen at Month 12 and Month 24 using a single dichotomous preference question
To measure participants' medical resource utilization under Q2M CAB LA + RPV LA compared to daily oral ART	• Medical resource utilization over 24 months • Clinic/hospital attendances • Rates of opportunistic infections and other illnesses
To assess programmatic acceptability of Q2M CAB LA + RPV LA	• Thematic analysis of data from interviews participants, healthcare workers and key stakeholders
To evaluate adherence to treatment	• Self-reported adherence and pill count for daily oral ART and delayed/missed injections for CAB LA + RPV LA
To evaluate drug levels	• Plasma concentrations of CAB LA and RPV LA

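### The resource-use endpoint is set over 24 months, but its questionnaire is last given at Month 18, so no resource-use questionnaire covers the final six months

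*Protocol article*

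**What the plan says.** Four places in the protocol article bear on this.

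- **Endpoint.** Table 3, under Objectives and endpoints, has an exploratory objective comparing resource use between the long-acting and daily oral arms. Its first endpoint is "Medical resource utilization over 24 months". Two further endpoints follow under the same objective, on attendances at clinic or hospital and on rates of opportunistic infections and other illnesses.
- **Questionnaire timing in the text.** The section Qualitative methods sub-study says: "All participants are asked to complete a brief questionnaire about medical resource utilisation at months 12 and 18 to support health economic analysis".
- **Questionnaire timing in the schedule.** In Table 2, under the block headed "Medical resource utilization and patient-related outcomes", the MRU row is marked at Baseline, Month 12 and Month 18. The Month 24 cell is empty.
- **Additional survey.** A Table 2 footnote adds: "Detailed healthcare resource data survey to be performed at Month 12 visit, at selected sites only".

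The Abstract fixes the horizon: "The total follow-up period is 24 months". Two other data streams run that far and overlap in part with resource use. The Clinical assessment section says "At every visit, participants are assessed for any interim AEs", and Table 3 has a secondary endpoint, "Incidence of HIV disease progression (HIV/AIDS-related hospitalizations, illness, or deaths) (through 24 months").

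**The concern.** The endpoint and its data collection stop at different times. A questionnaire completed at Month 18 cannot record what happens afterwards, whatever its recall period. The 24-month quantity therefore cannot come from the questionnaire alone. The analyst would have to extrapolate, draw on another source that the article does not name, or report a shorter period.

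The resource data also end at a different visit from the quality-of-life data. EQ-5D-5L is collected at Baseline and Months 6, 12 and 24. The resource questionnaire is collected at Baseline and Months 12 and 18. The two share only Baseline and Month 12, so an economic analysis that combines them would have components ending at Month 18 and Month 24. The article says that the questionnaire exists to support health economic analysis, and its Introduction presents the trial as evidence for policy. The period actually covered therefore matters to that use of the data.

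**Working it through.** **1. Read the schedule by cell position.** The MRU row of Table 2 was matched to the visit header column by column. Two other rows were read in the same way to check the alignment.

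| Row in Table 2 | Visits marked | Agreement with the text |
|---|---|---|
| MRU | Baseline, 12, 18 | Qualitative methods sub-study: 12 and 18 (Baseline not mentioned) |
| EuroQoL | Baseline, 6, 12, 24 | Qualitative methods sub-study: same visits |
| Vital signs | Both screening visits, Baseline, 1, 2, 3, 4, 6, 12, 18, 24, unscheduled | Clinical assessment: same, apart from the unscheduled visit |

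The check rows fall where the text says they should, so the empty Month 24 cell in the MRU row is not an effect of broken table layout. Text and table agree that the last collection is at Month 18.

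**2. Look for another resource-use instrument.** The only one is the detailed survey, at Month 12 and at selected sites. The Month 12 mark in the MRU row carries the letter g. Two footnotes are both labelled a, which shifts the later letters by one, so the matching text is printed under f. This survey adds nothing after Month 12.

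**3. Compute the gap.**

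- Endpoint period: 24 months (Table 3).
- Last questionnaire: Month 18.
- Gap: 24 − 18 = 6 months.
- Share of the period: 6 / 24 = 25%.

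**4. Ask what the questionnaire does cover.** The article gives no recall period, so coverage before Month 18 has to be assumed.

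| Assumed recall | Period covered | Not covered |
|---|---|---|
| Back to the previous collection | Months 0 to 18 | 6 / 24 = 25% |
| Six months | Months 6 to 18 | 12 / 24 = 50% |

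Both rows are illustrations. What they share is that Months 18 to 24 are not covered.

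**5. See what else is observed in Months 18 to 24.** Table 2 marks adverse events and concomitant medications at every visit through Month 24, and the HIV-progression endpoint also runs that far. These data can supply some hospital stays and illnesses. Attendances and other resource use not tied to an adverse event would not be reliably captured.

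**The case against.** The strongest reply is that the final six months are not dark. Adverse events and concomitant medications are recorded to Month 24, HIV-related hospital stays are an endpoint to Month 24, and the scheduled visits of each arm are fixed to Month 24. The article never says that the questionnaire is the only source for this endpoint. This is also a condensed article, and recall windows or supplementary sources may well stand in the full protocol. Finally, it is one line of an exploratory objective, with no hypothesis test or power claim.

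Much of this stands. A reader might infer that a quarter of follow-up is unobserved in all 540 planned participants, or that 24-month totals and between-arm differences will be understated by 25%. The documents support neither. The first ignores the data streams just listed. The second needs three things that the article does not state: that recall covers all of Months 0 to 18, that the questionnaire is the sole source, and that an 18-month total will be reported uncorrected as a 24-month one. It also needs a constant rate of use, and under a constant rate a rate per person-time would be unbiased and a total could be scaled up.

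What the reply does not remove is the conflict itself. The article prints both the period and the collection visits, and they do not match, so this is not a detail left to a fuller document. The other data are not named as the source for this endpoint. Using them only after Month 18 would change the method of measurement partway through.

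**Conclusion.** The point holds as an internal inconsistency of low severity. The 24-month endpoint in Table 3 outruns its only named participant-level instrument by 6 of 24 months. That figure rests only on the printed schedule and text, which agree with each other, and needs no assumption about recall.

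The size of any understatement of resource use cannot be derived from the article, because no recall period is given and the handling of the last six months is not described. The consequence is confined to what this exploratory endpoint can validly report. The primary comparison at Month 12 and the key secondary comparison of confirmed virologic failure are unaffected.

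**What to change.** Reconcile Table 2, Table 3 and the Qualitative methods sub-study section before the Month 24 analysis.

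1. **Where participants have not yet reached Month 24:** add the resource questionnaire at that visit, with recall back to the Month 18 visit. Both arms already attend at Month 24, and EQ-5D-5L and MOS-HIV are collected there. The cost is one brief questionnaire. The last participant was enrolled on 6 May 2024, so that person's Month 24 falls around May 2026. Whether this option is still open depends on when the change is made.
2. **Otherwise, one of two routes:** restate the questionnaire-based endpoint as covering 18 months, which is a small change of wording and works at any stage of the trial. Or name the adverse-event and serious-adverse-event records as the source for Months 18 to 24 and report that period separately, so that the two methods of measurement are not added into one total.

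In the same edit, state the recall period of the questionnaire, and mention in the text the Baseline collection that Table 2 shows.

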## Statistical Analysis Plan

### Primary Statistical Hypothesis

CAB LA + RPV LA is non-inferior (non-inferiority margin, -10%) in the proportion of participants with plasma HIV-1 RNA <50 c/mL as per FDA snapshot algorithm at Month 12, compared to a daily triple drug oral regimen consisting of 2NRTI + DTG regimen (ART).

Analysis will be undertaken to evaluate primary and secondary objectives of the protocol after all participants have completed their Month 12 visit, and undertaken again once all participants have completed their Month 24 visit. The primary analysis will be conducted using the Month 12 data. No adjustment for multiplicity resulting from repeated evaluation of the primary endpoint will be made, as the Month 24 analyses will be secondary.

For the primary efficacy endpoint analysis, each participant’s virologic response (HIV 1 RNA <50 c/mL) will be calculated according to the FDA’s snapshot algorithm. The primary analysis will be based on the intention to treat (ITT) analysis set. For the primary comparison, the adjusted estimate of the difference in the proportion of participants with virologic response between the 2 groups will be presented along with confidence intervals (CIs), based on an analysis stratified by study site using the Cochran Mantel-Haenszel Method (CMH). Treatment with CAB LA + RPV LA will be considered non-inferior to daily oral ART if the lower limit of the CMH-based 95% CI of the difference in virologic response between the treatment groups is >-10%. Should treatment with CAB LA+ RPV LA demonstrate non-inferiority to daily oral ART, an additional hypothesis testing on the superiority of CAB LA + RPV LA will be conducted. CAB LA+ RPV LA will be considered superior to daily oral ART if the lower limit of the CMH-based 95% CI of the difference in virologic response between the treatment groups is >0%. Since an analysis on the ITT analysis set may not be conservative in a non-inferiority setting, an analysis based on the PP analysis set will also be performed to investigate the impact of excluding participants with major protocol violations and evaluate the robustness of the primary analysis results.

The key secondary endpoint of CVF at Month 12 will be analysed to test the non-inferiority hypothesis. The adjusted estimate of the difference in the proportion of participants with CVF between the 2 groups will be presented along with CIs, based on an analysis stratified by study site using the CMH method. Treatment with CAB LA + RPV LA will be considered non-inferior to daily oral ART if the upper limit of the CMH-based 95% CI of the difference in CVF between the treatment groups is <4%. For virologic endpoints at Month 24, analyses will be conducted similarly as for Month 12.

The independent data safety monitoring committee (IDMC) will evaluate the interim efficacy, tolerability, and safety of CAB LA + RPV LA for this study. The IDMC will review safety data on a rolling 6-monthly interval. An interim futility analysis will take place once 50% of trial participants have data available on the primary virologic response outcome at Month 12. A Haybittle-Peto stopping rule will be pre-specified such that the trial will be stopped only if futility is demonstrated beyond reasonable doubt (i.e., P<0.001), with no adjustment made to the overall study level of significance for the final analysis (Alpha=0.05). The statistical analysis plan (SAP) will describe the planned interim analyses in greater detail, and additional details regarding the IDMC will be provided separately in the IDMC charter.

